## Abstract

The study examines the impact of the introduction of 10-valent Pneumococcal Conjugate Vaccine (PCV10) into Bangladesh’s national vaccine program. PCV10 is administered to children under 1 year-old; the scheduled ages of administration are at 6, 10, and 18 weeks.

The study is conducted in ~770,000 population containing ~90,000 <5 children in Sylhet, Bangladesh and has five objectives: 1) To collect data on community-based pre-PCV incidence rates of invasive pneumococcal diseases (IPD) in 0-59 month-old children in Sylhet, Bangladesh; 2) To evaluate the effectiveness of PCV10 introduction on Vaccine Type (VT) IPD in 3-59 month-old children using an incident case-control study design. Secondary aims include measuring the effects of PCV10 introduction on all IPD in 3-59 month-old children using case-control study design, and quantifying the emergence of Non Vaccine Type IPD; 3) To evaluate the effectiveness of PCV10 introduction on chest radiograph-confirmed pneumonia in children 3-35 months old using incident case-control study design. We will estimate the incidence trend of clinical and radiologically-confirmed pneumonia in 3-35 month-old children in the study area before and after introduction of PCV10; 4) To determine the feasibility and utility of lung ultrasound for the diagnosis of pediatric pneumonia in a large sample of children in a resource-limited setting. We will also evaluate the effectiveness of PCV10 introduction on ultrasound-confirmed pneumonia in 3-35 month-old children using an incident case-control design and to examine the incidence trend of ultrasound-confirmed pneumonia in 3-35 month-old children in the study area before and after PCV10 introduction; and 5) To determine the direct and indirect effects of vaccination status on nasopharyngeal colonization on VT pneumococci among children with pneumonia
**.  **

This paper presents the methodology. The study will allow us to conduct a comprehensive and robust assessment of the impact of national introduction of PCV10 on pneumococcal disease in Bangladesh.

## Introduction

Pneumonia is the leading cause of death among children 1–59 months of age globally
^1^. S
*treptococcus pneumoniae* (pneumococcus) is a major cause of childhood pneumonia and other invasive pediatric diseases including meningitis and sepsis, accounting for approximately 14.5 million cases of invasive pneumococcal disease (IPD) and 826,000 child deaths worldwide
^2^. Among these estimated deaths, 741,000 are pneumonia deaths and 60,500 are deaths due to meningitis
^2^. Bangladesh is one of the ten countries with the highest number of IPD cases and IPD-related deaths among children under 5 years of age
^2^.

Pneumococcal conjugate vaccines (PCVs) have been documented to be safe and effective for reducing illness and deaths caused by
*S. pneumoniae* in numerous studies. In most high-income countries, PCVs are used routinely, with a concomitant and substantial reduction of pneumococcal diseases
^3^,^5^. In 2006, the World Health Organization (WHO) recommended that PCV should be included in the routine infant immunization programs of all countries
^6^. Despite this recommendation, many low- and middle-income countries (LMICs) have not introduced the vaccine. The Global Alliance Vaccine Initiative (GAVI) co-financing has resulted in an increase in PCV introduction into national immunization programs of LMICs. The proportion of the world's birth cohort living in countries with PCV in national immunization programs has increased from 1% in 2000 to 31% in 2012
^7^. One hundred twenty eight countries have included PCV in their national immunization programs, however global coverage for completing all three doses of the vaccine were only 37% in 2015
^8^. This finding suggests that efforts to increase PCV introduction and use globally have made substantial progress; however, gaps in PCV use remain, particularly in Asia and in countries with large birth cohorts, where concerted efforts are required
^7^,^8^.

In 2013, the Ministry of Health and Family Welfare (MOHFW) of the Government of Bangladesh (GoB) decided to introduce 10-valent Pneumococcal Conjugate Vaccine (PCV10) into the national routine immunization program beginning in March 2015 making it the second South Asian country to implement PCV into routine childhood immunization, after Pakistan. In Bangladesh, the first dose of PCV10 is offered at 6 weeks of age along with pentavalent vaccine. The second and third doses are given at 10 and 18 weeks of age. Additionally, when the vaccine was introduced in March 2015, all infants who were less than 12 months old were offered the first dose of PCV10 and routine PCV10 immunization continued for this cohort. The decision to introduce PCV in Bangladesh in this way offered a unique and time-limited opportunity to generate pre-PCV data on pneumococcal diseases, and to conduct an impact assessment of PCV10 in the country following its introduction to measure its effect. Although Bangladesh had pre-PCV data on IPD from urban hospitals
^9^,^10^ allowing for before-after studies, population-based data were limited on culture-positive IPD from rural areas where the majority of child deaths are expected to occur
^11^.

We established community- and facility-based surveillance beginning January 1, 2014 to generate data on community-based pre-PCV IPD incidence rates in children 0–59 months of age in Sylhet district of Bangladesh. In addition to documenting the pre-PCV IPD rates in the study areas, the surveillance was designed to assess the feasibility of conducting an adequately powered IPD case-control study in our study population after vaccine introduction to estimate the impact of PCV10.

There are certain limitations of using IPD as the sole outcome when measuring the impact of PCV10. Many pneumococcal disease cases, particularly pneumonia cases, are not associated with bacteremia and therefore are not culture positive when testing for pneumococcus in the bloodstream
^12^,^14^. Thus, the etiology of community-acquired pneumonia can only rarely be determined by blood culture and relying on blood culture substantially underestimates pneumococcal disease burden. Widespread use of antibiotics in the community may further reduce the likelihood of positive results from blood culture. Although the point prevalence of clinical pneumonia among young children in Sylhet as determined by maternal report is fairly high at 4.9%, we expect to detect only about 50 IPD cases in our study area which contains about 90,000 <5 year old children in the year prior to PCV10 introduction
^15^. Therefore, it is important to consider other pneumococcal-related outcomes, albeit non-specific, when measuring the impact of PCV10 introduction. To provide a more complete assessment of the impact of the PCV10 vaccine, we are conducting a comprehensive impact assessment of PCV introduction in our population. We have designed this study to measure multiple outcomes including IPD, nasopharyngeal (NP) carriage, and both radiographically- and sonoraphically-confirmed pneumonia.

### Aims and objectives

The primary aim of this study is to conduct a comprehensive evaluation of the national introduction of the PCV10 in Bangladesh measuring multiple outcomes. To accomplish this aim, we have established the following objectives for the study:

**Objective 1:** To collect data on community-based pre-PCV incidence rates of IPD in children 0–59 months of age in Sylhet district of Bangladesh.

**Objective 2:** To evaluate the effectiveness of PCV10 introduction on Vaccine Type (VT) IPD in children 3–59 months of age using an incident case-control study design. Secondary aims include measuring the effects of PCV10 introduction on all IPD, regardless of serotype, in children 3–59 months of age using the case-control study design, and quantifying the emergence of Non Vaccine Type (NVT) IPD.

**Objective 3:** To evaluate the effectiveness of PCV10 introduction on chest radiograph-confirmed pneumonia in children 3–35 months of age using an incident case-control study design. An additional aim is to estimate the incidence trend of clinical and radiologically-confirmed pneumonia in 3–35 month-old children in the study area before and after introduction of the PCV10
** vaccine.

**Objective 4:** To determine the feasibility and utility of lung ultrasound for the diagnosis of pediatric pneumonia in a large sample of children in a resource-limited setting. We also sought to evaluate the effectiveness of PCV10 introduction on ultrasound-confirmed pneumonia in children 3–35 months of age using an incident case-control study design and to examine the incidence trend of ultrasound-confirmed pneumonia in 3–35 month-old children in the study area before and after introduction of the PCV10 vaccine.

**Objective 5:** To determine the direct and indirect effects of vaccination status on NP colonization on VT pneumococci among children with pneumonia.

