### Objective 2: IPD case-control and incident trend studies

We have maintained the IPD surveillance established for Objective 1 in our study area, including community surveillance, health facility activities and laboratory procedures, in order to detect IPD cases. The inclusion criteria for the case-control and incident trend studies are shown in
Table 3 and
Table 4. The age eligibility for enrollment in the IPD case-control study is shown in
Table 5 and the sample size requirement for IPD case-conrol study is shown in
Table 6.

**Table 3. T3:** Inclusion criteria for the IPD case-control study.

**Inclusion criteria**	1. Age 3–59 months meeting age-eligibility criteria under which they have had the potential to have started the PCV vaccine (not born yet or under age 12 months on March 25, 2015).
	2. Resident of the active surveillance area clinically eligible. a. For cases – clinically suspected invasive pneumococcal disease (pneumonia or meningitis or high fever) and pneumococcus isolated form blood or cerebrospinal fluid b. For controls-without any signs/symptoms of invasive pneumococcal disease as screened by physicians (hospital controls) or data collectors in the community (community controls)
	3. Written informed consent by parents/care givers.
**Exclusion criteria**	1. Refusal to join the study

**Table 4. T4:** Inclusion criteria for the incident-trend study.

**Inclusion criteria**	1. Age 3–59 months meeting age-eligibility criteria under which they have had the potential to have started the PCV vaccine (not born yet or under age 12 months on March 25, 2015).
	2. Resident of the active surveillance area
	3. Diagnosed clinically as invasive pneumococcal disease and pneumococcus isolated from blood or cerebrospinal fluid
	4. Written informed consent for participation in x-ray study by parents/care givers.
**Exclusion criteria**	1. Refusal to join the study

**Table 5. T5:** Age-eligibility criteria for inclusion in invasive pneumococcal diseases case-control study by study months. Age in completed months.

Year	2015					2016											
Month	Aug	Sep	Oct	Nov	Dec	Jan	Feb	Mar	Apr	May	Jun	Jul	Aug	Sep	Oct	Nov	Dec
Month of case- control study	1	2	3	4	5	6	7	8	9	10	11	12	13	14	15	16	17
Minimum age of eligibility	3	3	3	3	3	3	3	3	3	3	3	3	3	3	3	3	3
Maximum age of eligibility	15	16	17	18	19	20	21	22	23	24	25	26	27	28	29	30	31
Year	2017																
Month	Jan	Feb	Mar	Apr	May	Jun	Jul	Aug	Sep	Oct*	Nov*	Dec*	**If needed for adequate sample* *size*				

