### Objective 5: Assessment on the impact on NP carriage

An assessment of the baseline rates of NP pneumococcal colonization among participants with radiograph-confirmed pneumonia began following the start of the chest radiograph study in September 2015. Physicians collect nasopharyngeal swabs on all consenting clinical pneumonia cases. Participants are requested to sign a separate consent for NP swab collection. NP specimens are collected using nylon flocked swabs in accordance with updated WHO core methods
^28^,^29^. A single NP specimen is collected from the posterior nasopharynx of each subject by inserting the swab, rotating it 180 degrees and removing it. The swab is inserted immediately into one mL of liquid STGG transport medium and transported on ice to the clinical laboratory in Sylhet. Swabs are frozen at -20°C and stored for up to seven days. All swabs of confirmed radiographic pneumonia cases are cultured for pneumococcus; the remaining swabs are discarded. In the lab, the specimen are vortexed, aliquoted into two separate specimens (one with the swab retained), and a sample inoculated into broth for enrichment. Following broth enrichment, the sample is plated onto a gentamicin-blood agar plate and incubated in a CO2 incubator for isolation of pneumococcus. An aliquot of the broth enrichment as well as the remaining STGG NP sample are frozen (−80°C). Pneumococci are detected based on morphology, optochin susceptibility and bile solubility.

To determine the density of pneumococcal colonization, a second sample from the STGG vial is subjected to 10-fold dilutions up to 10
. An amount of 100 μl of each dilution is plated onto gentamicin blood agar plates and the semiquantitative results are documented, based on the numbers on the plates with countable number of pneumococcal and dilution factors. Pneumococcal strains are serotyped by the capsular swelling procedure (quellung reaction) with type-specific anti-pneumococcal omni, pool, type or group, and factor sera (Statens Seruminstitute, Copenhagen, Denmark).

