***Objective 5:*** The primary study outcome will be prevalence of vaccine-type pneumococci (serotypes 1, 4, 5, 6B, 7F, 9V, 14, 18C, 19F, and 23F) among children with radiographically-confirmed pneumonia, stratified by vaccination status. We will calculate this prevalence rate for all children with X-ray confirmed pneumonia during a rolling calendar period, beginning the first week of NP swab collection. Standard deviations and 95% confidence intervals for the prevalence rates will be calculated. Rates will be calculated both unadjusted and adjusted for participant demographic characteristics. Rates will be plotted against time separately for vaccinated and unvaccinated participants using the midpoint of the interval as the time point shown on the x-axis, and with population prevalence of immunization superimposed, as in Loughlin
*et al.* (2014)
^32^.

In a secondary analysis, we will use a multivariate logistic regression model to test the effect of time trend, vaccination status and the interaction of time and vaccination status on carriage of VT pneumococci in this population of pediatric Bangladeshi pneumonia patients. Other analyses may explore the joint effect of vaccination status and time on carriage of NVT pneumococci.

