## Discussion

The GoB MOHFW introduced PCV10 on March 2015, making it the second South Asian country to add PCV to their national vaccine schedule. While developed countries have seen significant decreases in pneumococcal disease after the introduction of PCV vaccines, there are a number of challenges that should be considered when introducing a new vaccine in resource poor settings such as in Bangladesh
^33^,^37^. First, pneumococcus has over 90 different serotypes, and the currently licensed vaccines contain only either 10 or 13 of the different serotypes. Additionally, the serotype distribution of the pneumococci that cause disease varies by location, and some countries have observed serotype replacement
^38^,^40^. GAVI currently provides co-funding for the introduction of vaccines such as PCV. Countries such as Bangladesh will be required to bear the financial burden for the implementation of all the vaccines including PCV, which is very expensive. Because of these issues, the WHO recommends that all countries have an assessment of the introduction of PCV10 to determine its impact in each setting.

The Pneumococcal Conjugate Vaccine Impact Study, expected to be completed in mid-2018, is a prospective community- and facility-based observational cohort study with a variety of nested studies including case-control and pre-post studies to evaluate the impact of PCV10 in Bangladesh. We designed a comprehensive, multiple outcome impact assessment because each outcome has its own strengths and drawbacks. Classic impact assessments generally measure and compare rates of IPD in vaccinated and unvaccinated children. However, there are several limitations to such a design. For example, not all IPD is associated with bacteremia, and the majority of cases of pneumococcal pneumonia are blood culture negative
^41^. Therefore, estimating the impact of vaccine on IPD alone will underestimate the burden of pneumococcal disease and will underestimate the true value of the vaccine. Additionally, many children arrive at health facilities with recent or current antibiotic use, increasing the difficulty to isolate pneumococcus in the lab from their specimen
^42^. To account for the attenuated estimate expected when measuring IPD rates and to get a more complete assessment of the impact of PCV10 in our population, we have considered 3 additional outcomes: 1) chest radiograph-confirmed pneumonia; 2) lung ultrasound-confirmed pneumonia; and 3) NP carriage.

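### Objective 5 promises the indirect effect of PCV10 on vaccine-type carriage, but swabbing starts about 5 to 6 months after launch with no pre-vaccine reference, so the plan can estimate only change since the first swab

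*Protocol article*

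**What the plan says.** All references are to the protocol article.

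- **Aim.** Under Aims and objectives, Objective 5 is "To determine the direct and indirect effects of vaccination status on NP colonization on VT pneumococci among children with pneumonia". The Discussion explains the indirect part as herd immunity: less circulation of the organism protects unimmunized children in the same community.
- **Launch.** The Introduction says that "when the vaccine was introduced in March 2015, all infants who were less than 12 months old were offered the first dose of PCV10". The eligibility criteria for the IPD studies use a specific day: "not born yet or under age 12 months on March 25, 2015".
- **Swabs.** The Objective 5 section describes "An assessment of the baseline rates of NP pneumococcal colonization" in radiograph-confirmed cases, which "began following the start of the chest radiograph study in September 2015".
- **Analysis.** In the analysis plan, the primary Objective 5 outcome is vaccine-type (VT) prevalence by vaccination status. It is computed over a rolling calendar window that opens with the first week of swabbing and plotted against time, with population coverage overlaid. The secondary logistic model is used "to test the effect of time trend, vaccination status and the interaction of time and vaccination status on carriage of VT pneumococci".
- **Other data.** The surveillance that began in January 2014 is described for IPD rates, not carriage. No pre-vaccine or external carriage comparator is described. Coverage surveys took place in August-September 2016 and 2017, and a union-month Poisson regression on coverage is planned for disease incidence.

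**The concern.** The indirect effect on carriage is the fall in VT carriage among unvaccinated children that results from vaccinating others, so it needs a reference with no vaccination in the population. This design does not have one. The first swabs come from a population in which roll-out, including the catch-up offer, had been running for months.

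In the model, the indirect effect can be read only from the time trend in unvaccinated children, and time starts at the first swab. Any fall before then is absorbed into the starting level. Calling that level baseline invites readers to take it as pre-vaccine. A flat trend could then be reported to the Ministry, the study's main stakeholder, as a lack of herd protection when the data cannot show that.

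**Working it through.** Objective 5 states no sample size, power or effect size, so there is no figure of the plan's own to reproduce. The check uses dates, Table 8 and a sensitivity calculation.

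**1. Launch to first swab.** From 25 March 2015 (eligibility date) to 1 September 2015 is 160 days, and to 30 September it is 189 days. At 30.4375 days per month, 160/30.4375 = 5.3 and 189/30.4375 = 6.2 months.

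**2. Share of the age group already eligible.** Radiographs are taken at 3-35 months. For September 2015, Table 8 gives eligible ages of 3 to 16 completed months: (16 - 3 + 1)/(35 - 3 + 1) = 14/33 = 42% of the monthly age bands.

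**3. Share already vaccinated.** The document gives no coverage figure for September 2015. Table 9's 46% is a planning value for the case-control studies as a whole.
- If 46% applied at once among eligible children: 0.424 × 0.46 = 20% of 3-35 month-olds.
- If 46% were an average on a straight line rising to an assumed 80%, the start would be 2 × 0.46 - 0.80 = 12%, and 0.424 × 0.12 = 5%.
- At an assumed 90% uptake: 0.424 × 0.90 = 38%.

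The starting population was partly vaccinated, but to an unknown degree.

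**4. Share of the indirect effect that precedes the first swab.** Let s = 5.3 to 6.2 months and T = 33.2 months (launch to December 2017, the last month in Table 8, taken as the end of follow-up). The document gives no carriage trend, so every shape of decline in log-odds among unvaccinated children is an assumption.

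| Assumed decline | Formula | Missed share |
|---|---|---|
| 6-month lag, then linear | max(0, s - 6)/(T - 6) | 0-1% |
| 3-month lag, then linear | (s - 3)/(T - 3) | 8-11% |
| Linear from launch | s/T | 16-19% |
| Exponential, half-life 12 months | (1 - 0.5^(s/12))/(1 - 0.5^(T/12)) | 31-35% |
| Exponential, half-life 6 months | (1 - 0.5^(s/6))/(1 - 0.5^(T/6)) | 47-52% |

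As an illustration, a true indirect odds ratio of 0.50 would appear as 0.50^0.84 = 0.56 to 0.50^0.81 = 0.57 under the linear shape, and as 0.50^0.50 = 0.71 if half the decline came first.

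**5. Who the unvaccinated children are.** In September 2015, 19 of the 33 age bands (17 to 35 months) had never been eligible. From April 2017 Table 8 sets the maximum at 35 months, so all 33 bands are eligible. Over the series the unvaccinated group therefore changes from mainly older, never-eligible children to eligible children who missed vaccination. That shift, season and secular change all enter the time trend and can move it either way.

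**6. Start dates.** The Objective 3 section puts the start of the radiograph case-control study two months after introduction (about May 2015), Table 8 has August 2015 as month 1, and the Objective 5 section gives September 2015 for the radiograph study. The figures in steps 1 and 2 depend on which date is right, but every version falls after launch.

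**The case against.** The best defence is that the primary analysis is descriptive. It plots VT prevalence in vaccinated and unvaccinated children with coverage overlaid, so a reader sees how far roll-out had gone at the first window. The analysis text does not use the word baseline and does not treat that window as zero coverage. A coverage covariate is also model detail that an article may leave to a fuller plan. One area-wide coverage value per month is almost a function of calendar time, so adding it would identify little. Herd effects may lag, in which case little is lost.

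Much of this stands. The lag argument is sound: step 4 gives about zero at six months. The collinearity argument is sound too, which is why the coverage term should vary by union and not only by month. An overlay, however, is not an estimate and supplies no zero-coverage reference. The objective, the baseline label, the time origin and the model terms are all fixed in this document, and they do not fit together. The protocol already plans union-month coverage regression for incidence, so the method is within the study's reach.

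**Conclusion.** The point holds as a mismatch between the stated aim and what the plan can estimate. The time trend in unvaccinated children is change since the first swab, and any indirect effect in the 5 to 6 months before it is missed. This rests on dates and model terms in the document and on the absence of any described pre-vaccine carriage data.

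Three stronger readings are not supported:

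- **That the indirect effect is understated by a known amount.** September 2015 coverage, the shape of the decline and the lag are all missing. The range of about zero to about half in step 4 comes from assumptions, not from an estimate of the loss.
- **That the time trend is at least a lower bound.** Season, secular change and the shifting age and eligibility mix could make it overstate the indirect effect.
- **That the direct effect fails too.** The contrast between vaccinated and unvaccinated children is not affected by the late start in the same way.

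**What to change.** 1. **Wording.** Call the September 2015 data early post-introduction rather than baseline. State in Objective 5 and its analysis that the time trend in unvaccinated children is change since first swab, that it is neither the full indirect effect nor a lower bound for it, and that a flat trend is not evidence of no herd protection.
2. **Model.** For unvaccinated children, add union-month PCV10 coverage to the carriage model, rebuilt from the 2016 and 2017 coverage surveys where dose dates allow, with adjustment for age, season and calendar time. Report the odds ratio per 10 points of coverage, and label any contrast with zero coverage as extrapolation.
3. **Dates.** Reconcile the start of the radiograph study across the Objective 3 text, Table 8 and the Objective 5 section.

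Items 1 and 3 cost only text. Item 2 uses data that the study already collects, but precision will be limited: it relies on 2015 coverage reconstructed from later surveys, whose stated union-level precision (within ten percentage points) is for children under 24 months. Fieldwork for Objective 5 is reported complete, so only analysis and wording can still change.
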